## Abstract

**Background:**

Stroke is a leading cause of death and disability internationally. One of the three effective interventions in the acute phase of stroke care is thrombolytic therapy with tissue plasminogen activator (tPA), if given within 4.5 hours of onset to appropriate cases of ischaemic stroke.

**Objectives:**

To test the effectiveness of a multi-component multidisciplinary collaborative approach compared to usual care as a strategy for increasing thrombolysis rates for all stroke patients at intervention hospitals, while maintaining accepted benchmarks for low rates of intracranial haemorrhage and high rates of functional outcomes for both groups at three months.

**Methods and design:**

A cluster randomised controlled trial of 20 hospitals across 3 Australian states with 2 groups: multi- component multidisciplinary collaborative intervention as the experimental group and usual care as the control group. The intervention is based on behavioural theory and analysis of the steps, roles and barriers relating to rapid assessment for thrombolysis eligibility; it involves a comprehensive range of strategies addressing individual-level and system-level change at each site. The primary outcome is the difference in tPA rates between the two groups post-intervention. The secondary outcome is the proportion of tPA treated patients in both groups with good functional outcomes (modified Rankin Score (mRS <2) and the proportion with intracranial haemorrhage (mRS ≥2), compared to international benchmarks.

**Discussion:**

TIPS will trial a comprehensive, multi-component and multidisciplinary collaborative approach to improving thrombolysis rates at multiple sites. The trial has the potential to identify methods for optimal care which can be implemented for stroke patients during the acute phase. Study findings will include barriers and solutions to effective thrombolysis implementation and trial outcomes will be published whether significant or not.

**Trial registration:**

Australian New Zealand Clinical Trials Registry: ACTRN12613000939796

## Background

### Effective treatments for stroke can provide major reductions in health burden

Stroke is a major cause of death and disability internationally, with over 5 million deaths from stroke worldwide [1]. Stroke accounted for approximately 1 in every 19 deaths in the United States in 2009 [2], with US projections indicating that an additional 4 million people will have had a stroke by 2030 [3], a 22% increase in prevalence from 2013 [4]. The mean cost per person for stroke care in the United States in 2009 was estimated at $6,018 [5]. In 2009, The Australian Bureau of Statistics reports an estimated 381,400 Australians (1.8% of the total population) had suffered a stroke [6], with 35% reporting at least one impairment as a result of that stroke [6] and 62% of these reporting their stroke as their main disabling condition [6]. Stroke was the underlying cause of death for 11,220 Australians in 2010 [6] and is the second leading cause of death and a leading cause of long-term disability [7]. In 2012, the total financial cost of stroke was around $5 billion [8] with an estimated burden of disease cost of $49.3 billion [8]. In 2012, there were nearly 50,000 strokes in Australia, with approximately 12,000 people dying as a result of their stroke [8]. In 2009 to 2010, 35,345 hospitalisations were recorded in Australia with a principal diagnosis of stroke [9] and an average length of stay of 9 days [9]. The majority of strokes (89%) are admitted to hospital [10], and approximately 50% of sufferers are left either deceased or dependent [11].

Improved outcomes for acute stroke can be achieved by: use of aspirin within 48 hours to provide a modest absolute risk reduction of 1% [12]; Stroke Care Units (SCU) [13]; and thrombolytic therapy using intravenous tissue plasminogen activator (tPA) administered to appropriate patients according to guidelines and within 4.5 hours of symptom onset [14,15]. A systematic review of randomised trials of intravenous tPA within 6 hours of acute ischaemic stroke onset found intravenous tPA significantly increased the odds of being alive and independent (modified Rankin Scale of 0 to 2) at 3-month follow-up for those treated within 3 hours of onset [16]. Sustained improvements in functional outcome and health-related quality of life have been identified at up to 18-month follow-up [17]. Treatment benefits for tPA are highest if administered within 3 hours of stroke onset [16,18,19] but can extend beyond the 3-hour window [20], with tPA considered safe for eligible patients up to 4.5 hours after stroke onset [21]. The ‘number needed to treat’ with tPA to prevent death and dependency is between 6 and 14, but may be higher depending on the favourable outcome definition and method of calculation [15,22,23]. Although there has been some debate about the strength of the evidence provided by thrombolysis [24,25], the treatment is endorsed via national and international guidelines [26-29].

### Thrombolysis is a cost-effective stroke treatment when used appropriately

Cost-effectiveness analyses have indicated that high-cost treatments for acute stroke can provide major public health benefits even when minor reductions in disability are achieved [30]. A number of studies have identified thrombolysis as being a cost-effective treatment when used appropriately [31-34]. A UK study estimated that over a lifetime, tPA was associated with cost-savings of £96,565 per quality-adjusted life year [33]. The Model of Resource Utilization, Costs, and Outcomes for Stroke (MORUCOS) study found that tPA saved 155 disability-adjusted life years in a group of 256 eligible patients and concluded that tPA is more effective and cost-saving than treatment with aspirin [32].

### Rates of thrombolysis remain low internationally

Despite evidence for the cost-effectiveness and safety of thrombolysis along with international recommendations being in place for a number of years [21,35,36], there has been little overall growth in thrombolysis rates. Thrombolysis rates have remained relatively low in a number of countries over the past decade: In the US, tPA administration rates increased from 0.87% in 2001 to 2.40% in 2006 [37]. In the UK in 2008, while an estimated 26% of acute stroke patients were eligible for thrombolysis, only 1.4% were administered the treatment [38]. Only 4.3% of ischemic stroke patients in the California Acute Stroke Pilot Registry received thrombolysis [3]. In Australia, despite making major progress in terms of wide establishment of stroke care units, tPA rates are approximately 7% [30].

### Achieving large-scale increases in rates of thrombolysis is challenging

Changing practice is an acknowledged challenge in a number of settings [39]. Improving rates of thrombolysis delivery, even after medical treatment has been sought, involves challenges at several levels, including paramedic recognition of stroke prior to hospital arrival, attendance at a tPA-capable hospital, prompt triaging from the Emergency Department to a Stroke Care Team, rapid access to CT or MRI scan to establish ischaemic stroke, and the availability of appropriately-trained clinicians to provide tPA. A description of the series of tasks involved in the delivery of timely thrombolysis (see Table 1) illustrates the number of tasks, complexity, multidisciplinary nature, and time urgency involved in successful delivery of thrombolysis for acute stroke. An Australian study at a single large teaching hospital (Pre-hospital Acute Stroke Triage [PAST]) developed and implemented a pre-hospital stroke assessment tool for ambulance officers and a pre-hospital notification system following assessment of system barriers [40]. The PAST study demonstrated an increase in tPA rates from 4.7% to 21.4% [40].

**Table 1 T1:** Framework for situational analysis exploring phases of care, tasks, staff roles and time frames

**Phase**	**Task**	**Staff**	**Time frame**
**1. Pre-hospital assessment**	*Assess potential tPA eligibility*	Paramedic	<2 h of onset
	Whether probable stroke or stroke mimic, define time of onset, consider comorbidity/frailty, estimate for survival		
	Deliver to tPA-capable hospital	Paramedic	
	Handover to triage or Acute Stroke Team	to ED/SCU	
**2. Triage**	*Assess tPA eligibility*	ED or SCU	<3.5 h of onset
	Onset time, collateral history, mRS, anticoagulants, seizure, serious or advanced terminal illness, history of intracranial haemorrhage or subarachnoid haemorrhage, major internal surgery in last 21 days, heart attack with IV thrombolysis in last 72 hours, stroke severity assessment with National Institutes of Health Stroke Scale, Glasgow Coma Scale, observations		
	Handover to SCU	to Acute Stroke Team	
**3. Clinical assessment**	*Assess tPA eligibility*	SCU Nurse	
	Onset time certainty, functional independence, comorbidity, current medication, relative and absolute contraindications, NIHSS score, collect blood, notify CT scanning & organise transport, organise ECG		
	Handover to Imaging	to Radiography	
**4. Imaging**	Non- contrast CT scan (or perfusion CT or MRI)	Radiography	
	Handover to SCU	to SCU Nurse	
**5. Final clinical assessment**	*Confirm tPA eligibility*	SCU Medical	
	Review information from phase 1-3, focussed history to check for stroke mimic, onset certainty, premorbid functional independence, medication, contraindications, NIHSS, rapid cardiac and vascular screen, check blood sent to lab, review ECG, review NCCT on console with radiographer and again for degree of ischaemic change & possibility of stroke mimic, discuss scenarios with patient and family		
**6. Preparation & delivery**	*tPA Preparation*	SCU Nurse	<4.5 h of onset
	Check serum glucose level, anticoagulant medication, International Normalized Ratio, Blood Pressure, NIHSS.		
	Treat serum glucose or Blood Pressure if necessary and reassess	SCU Nurse	
	Administer thrombolysis, with amount based on estimated patient weight	SCU Nurse	
**7. Monitor**	Monitor and manage neurological status (NIHSS at 0 h, 1 h, 24 hrs), blood pressure and serum glucose level	SCU/ICU staff	24 h from tPA delivery

Achieving multi-site change in thrombolysis rates for acute stroke poses an even more complex challenge, with very few published trials. One study looked at the benefits and challenges of establishing stroke units [41], and two trials have explored thrombolysis in particular. The US Get-With-The Guidelines stroke project – a national quality improvement program – demonstrated an increase in adherence to guideline recommendations for stroke from a baseline rate for intravenous thrombolytics of 42.09% to 72.84% in the fifth year of the project [42]. The PRomoting ACute Thrombolysis in Ischemic StrokE (PRACTISE) cluster randomised trial in The Netherlands used the Breakthrough approach – a quality improvement methodology using Plan-Do-Study-Act (PDSA) cycles – to change clinical practice [43]. The PRACTISE trial found that a significantly higher proportion of intervention group ischemic stroke patients presenting within four hours of stroke onset were thrombolysed (44.5%) compared to ischemic stroke patients in the control group (39.3%) [43]. However, patients in the intervention group experienced higher post-care dependency [43]. The PRACTISE trial authors suggested a need for a more intense intervention with continuous process measures to achieve more substantial improvements in thrombolysis rates [43]. Studies of the Breakthrough approach in other settings have produced mixed results [44,45], which may suggest the need for additional strategies or a more intensive approach in order to achieve sustained change in complex systems. The INSTINCT cluster randomised controlled trial [46] of 24 acute-care community hospitals in the US used a multilevel, barrier assessment-interactive educational intervention. The intervention included educational elements, assessment of barriers, audit and feedback. Trial results indicated a modest increase in the proportion of admitted stoke patients receiving thrombolysis between pre- and post-intervention periods (1.25% and 2.79% at intervention hospitals, compared to 1.25% and 2.10% at control hospitals using Intention to Treat analysis) but showed non-significant differences between groups. The authors concluded that additional strategies are needed in order to increase acute stroke treatment.

Therefore, a need remains for a rigorous trial of usual approaches versus a comprehensive and intensive strategy for increasing thrombolysis rates in a manner suitable for large scale implementation. The Thrombolysis ImPlementation in Stroke (TIPS) study aims to provide a robust test of a theory and evidence-driven multi-component and multidisciplinary collaborative approach designed to achieve sustained change in complex health systems over multiple sites.

## Aims

The study aims to test, using a cluster randomised controlled trial, whether a multi-component multidisciplinary collaborative approach can:

1. Increase the proportion of all stroke patients receiving thrombolysis at intervention hospitals, compared with control hospitals at follow-up (Primary Outcome);

2. Maintain best-practice benchmarks of 30% of patients achieving 3-month post-stroke modified Rankin scores of 0 to 1 (little or no disability) at both intervention and control sites (Secondary Outcome);

3. Ensure that the adverse event rate for major intracranial haemorrhage (parenchymal haematoma) in thrombolysed patients does not rise above best-practice benchmarks of 6% [19] in either intervention or control hospitals (Secondary Outcome).

## Methods and design

The cluster randomised controlled trial will involve 20 hospitals in the Eastern Australian states of New South Wales (NSW), Victoria (VIC) and Queensland (QLD). Hospitals are the unit of randomisation and the unit of analysis. SCUs manage the majority of stroke patients across the Eastern states of Australia. Hospitals in the intervention group will receive a multicomponent multidisciplinary collaborative intervention based on behavioural principles as described by the Behaviour Change Wheel framework for the design and implementation of evidence-based practice [47]. The control hospitals will receive no intervention and are free to make practice changes of their own accord. Thus the study is an implementation effectiveness trial rather than an efficacy trial. The follow-up period will be two years post-baseline (*i.e*., Year 1 to 2 = baseline, Year 3 = intervention, Year 4 = follow-up), with an additional three months for measurement of functional outcomes for those thrombolysed in the final month of follow-up. Figure 1 describes the study design.

**Figure 1 F1:**
[figure not shown]
Study design & timeframe.

### Sample

#### Inclusion criteria

Eligible hospitals are those with a Stroke Care Unit or staffing equivalent of a stroke physician and stroke nurse; an Emergency Department and where the hospital is at early stages of thrombolysis implementation. All participating hospitals are required to record every consecutive case of stroke and thrombolysis, including adverse events and patient functional outcomes at three months. Both public and private hospitals are eligible to be included in the sample, as are both teaching and non-teaching hospitals.

##### *Stratified* randomisation

Hospitals will be stratified according to their stroke thrombolysis rates at baseline: very low (0% to ≤4.00%), low (>4.00% to ≤10.00%) or moderate (>10.00%). Baseline thrombolysis rate was considered important for the following reasons: A ‘very low’ thrombolysis rate suggests some impediments to thrombolysis, potentially limiting the ability of the site to respond quickly to the intervention. Sites categorised as having a ‘low’ thrombolysis rate may have the greatest potential for achieving change during the study, due to having substantial room for improvement. Conversely, a site with a ‘moderate’ baseline rate of thrombolysis may have limited opportunity to demonstrate further substantial improvement on the outcome measure.

Hospitals will be randomised at one time (effectively achieving allocation concealment) to either the intervention arm or the control arm with a 1:1 allocation ratio, using a computer generated stratified randomisation scheme in StatsDirect. Intervention hospital staff will not be effectively blinded to their allocation, in that they will be aware of their own involvement in intervention activities. There will be minimal interaction with control hospitals during the intervention phase.

### Procedure

#### Site recruitment

Eligible hospitals were identified from National Stroke Foundation (NSF) audit records and state-based clinical SCU networks. Clinical leaders in stroke at each potentially eligible hospital have been contacted by a clinical leader from the research team to verify eligibility and have been invited in person or by telephone to provide in-principle support to participate in the study following discussions with relevant decision makers at each site. A signed memorandum of understanding or equivalent consent agreement between each hospital and the research team has documented agreement by all relevant parties to collaborate for the whole period of the study. Ethical approval for the study has been obtained from relevant human research ethics committees in each state, from each participating hospital and from The University of Newcastle Human Research Ethics Committee.

#### Data collection

Information on each patient thrombolysed during the study period will be entered into the secure TIPS database hosted on the National Stroke Foundation (NSF) website. Stroke imaging will be entered via an additional INternational Stroke Perfusion Imaging REgistry (INSPIRE) website designed for imaging data that will be linked to the TIPS database. The TIPS database is only accessible via secure logins and will be maintained by the NSF. The patient data will be entered by the stroke care nurse at each participating hospital as de-identified patient unit record data. Data quality including range checks will be undertaken. The research team will not have access to identifying information about individual clinicians, hospital staff, or data identifying individual patients other than in the normal course of their existing clinical duties. Electronic data files will be securely protected so that only the principal researchers will have access to these data. Staff members from participating departments at each hospital will be asked to complete an anonymous baseline voluntary survey regarding perceived barriers and facilitators to thrombolysis implementation at their hospitals. This survey will be repeated at follow-up.

### Measures

#### Primary outcome

Numerator: The numerator is the number of cases treated with thrombolytic therapy in each hospital. The following details will be recorded for each thrombolysed case: age, gender, date and time of stroke onset, date and time of arrival at treating hospital, date and time of brain imaging examination, time of tPA treatment, mRS grade before stroke (premorbid mRS), stroke severity (NIHSS Scale), hypertension, diabetes, hyperlipidaemia, smoking status (current or previous), previous diagnosis of stroke, atrial fibrillation (including paroxysmal), congestive heart failure, aspirin at stroke onset, dipyridamole at stroke onset, clopidogrel at stroke onset, anticoagulants (oral) at stroke onset, glucose level before treatment, and mRS at three months post-treatment. Patient imaging data will be uploaded via the INSPIRE database and will include: non-contrast CT (NCCT), perfusion CT (CTP), CT angiography (CTA), and Magnetic Resonance Imaging (MRI).

Denominator: The denominator is the number of cases with a primary discharge diagnosis code of stroke (ICD-10-AM I60.9, I61, I63, I64) that will be extracted from hospital records. The accuracy of ICD coding for all types of stroke is good [48-51], with a NSW tertiary hospital reporting 96% accuracy in stroke discharge diagnosis identified by a random selection of stroke medical records [50,51]. Another Australian study reported high levels of reliability and adherence to coding standard for ICD-10 codes [52], with a study of stroke attack rates and case fatality in the Hunter Region reporting 97.5% accuracy between stroke coding and audit [53]. Validation of Australian data sets for stroke diagnosis found 93% coding accuracy levels [49], and a Canadian study reported 92% coding accuracy using ICD-10 codes for stroke [54].

The primary outcome is the stroke thrombolysis rate for each hospital, calculated as the number of stroke cases thrombolysed divided by the total number of individuals with a stroke primary discharge diagnosis.

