### Key study limitations and challenges

#### Measurement of primary outcome – tPA rates

The measurements of both the numerator and denominator for the primary outcome are challenging. The study numerator is entered by the participating site, rather than by an independent, blinded auditor, therefore introducing potential bias. The study denominator – medical coding of all stroke cases – is independent and blinded in that medical coders at each hospital are unaware of the project. The denominator is also an approximation in that it includes all stroke cases rather than only ischaemic stroke cases.

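### The primary denominator lists one sub-code (I60.9) beside three whole stroke categories and counts cases in one sentence, individuals in another: a small effect, but a rule to correct

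*Protocol article*

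**What the plan says.** The code list is in the protocol article under Measures, Primary outcome: "The denominator is the number of cases with a primary discharge diagnosis code of stroke (ICD-10-AM I60.9, I61, I63, I64". The same section defines the numerator: "The numerator is the number of cases treated with thrombolytic therapy in each hospital". It closes with the outcome itself, the hospital's thrombolysis rate: "the number of stroke cases thrombolysed divided by the total number of individuals with a stroke primary discharge diagnosis". This last sentence repeats no codes and changes the unit from cases to individuals.

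Two other places describe the intended scope. The first aim is worded: "Increase the proportion of all stroke patients receiving thrombolysis at intervention hospitals, compared with control hospitals at follow-up (Primary Outcome". The limitations section on measurement of tPA rates says: "The denominator is also an approximation in that it includes all stroke cases rather than only ischaemic stroke cases".

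The baseline thrombolysis rate is also used to stratify hospitals, with cut points at 4.00% and 10.00% (Stratified randomisation). It is the adjustment variable in the primary analysis, and it defines the subgroup analysis that leaves out hospitals above 10% (Statistical methods).

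**The concern.** The four codes are not at the same level. I61, I63 and I64 each take in a whole category, while I60.9 takes in one member of its category. Two hospitals with identical patients and identical treatment can then report different rates, because one codes its I60 admissions to a specific fourth character and the other leaves them at 9. On the standard meaning of the code, which the article does not spell out, I60.9 is subarachnoid haemorrhage with the site unspecified. Inclusion would then turn on how fully the coder described the bleed.

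The change from cases to individuals is a second, smaller ambiguity. It leaves open whether a person admitted twice to the same hospital with stroke in one period counts once or twice, and whether numerator and denominator treat that person alike.

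This is a stated rule for the primary outcome, so an analyst who follows the article would extract the listed codes. At stake are some avoidable variation in a cluster-level outcome with only 10 hospitals per group, and the placing of hospitals that lie close to a stratum boundary.

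**Working it through.** **Scope, side by side.** The aim refers to all stroke patients and the limitations section to all stroke cases. The list admits I60 only at .9. If all of I60 was meant, the list is too narrow. If I60 was not meant, I60.9 should not be there. If I60.9 alone was meant, the article gives no reason. The coding-accuracy percentages cited in the Primary outcome section (92% to 97.5%) are given for stroke diagnosis or stroke coding in general; none is reported for fourth-character detail.

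**Unit.** The rate is calculated per hospital. Within one hospital, cases and individuals differ only when the same person is admitted more than once.

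**Inputs.** From Sample size: about 150 stroke patients per hospital per year, a control rate of 5%, a coefficient of variation of 0.4, and a detectable difference of 7 to 10 points. A rate of 12% is the control rate plus the lower planned difference (5 + 7). The article gives no figure for the share of I60 admissions coded other than .9, or for repeat admissions, so the shares below are assumptions. There is no plan figure to reproduce.

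**Effect on one hospital's rate.** Observed rate = treated / (150 − omitted).

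| Omitted | Share of 150 | True 12.0% (18 treated) | True 5.0% (7.5 treated on average) |
|---|---|---|---|
| 5 | 3.3% | 18/145 = 12.4% | 7.5/145 = 5.2% |
| 8 | 5.3% | 18/142 = 12.7% | 7.5/142 = 5.3% |
| 15 | 10% | 18/135 = 13.3% | 7.5/135 = 5.6% |

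Even a 10% omission moves the rate by only 1.3 points at 12% and 0.6 points at 5%. Counting persons instead of admissions shrinks the denominator in the same way, so the table serves for repeat admissions too.

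**Deliberate worst case between arms.** Suppose the denominator were 10% larger in one arm only. The spurious difference is 5 − 5/1.1 = 0.45 points at 5%, and 12 − 12/1.1 = 1.1 points at 12%. For the denominator alone to turn 5% into 12%, it would have to fall by 1 − 5/12 = 58%.

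**Noise.** Suppose the affected share varied between hospitals with a standard deviation of about 0.05, independently of the true rate. The coefficient of variation would go from 0.40 to √(0.40² + 0.05²) = 0.403. The planning value was taken from baseline data and may already contain this variation.

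**Cut points.** A single record matters only at the boundary, shown here with one year's 150 cases:
- 6/150 = 4.00% is very low; 6/149 = 4.03% is low.
- 15/150 = 10.00% is low and stays in the subgroup analysis; 15/149 = 10.07% is moderate and leaves it.

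**The case against.** The best defence is that this is loose wording in a condensed article. I60.9 may be shorthand or a deliberate choice, and detailed counting rules may stand in a fuller document that is not shown. Statistical methods says the denominator comes from computerised admissions data, which points to the admission as the unit. The rule is the same in both arms, the coding is described as "independent and blinded in that medical coders at each hospital are unaware of the project", and stratification and adjustment on the baseline rate absorb at least part of any stable coding difference between hospitals. All of this stands as to size and bias. It does not remove the mismatch, because the article does not leave the code list open: it prints one that disagrees with its own stated scope.

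A reader might infer more, and the documents do not support it:

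- **That the wording causes transferred patients to be miscounted.** A patient transferred in is one case and also one individual at the receiving hospital, so the change of unit has no bearing on transfers. The article does not mention transfers in this rate. Removing such records from the denominator alone would leave any of them treated at the receiving hospital in the numerator.
- **That the limitations section treats an ischaemic denominator as unobtainable.** It only discloses that the all-stroke denominator is an approximation, and all stroke is the declared aim. A rate on I63 and I64 would not fully cure that either, since I64 on its standard meaning is stroke of unspecified type.
- **That the rate reflects coding rather than treatment.** The arithmetic above rules this out at any plausible share.

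**Conclusion.** The inconsistency is real and sits in the definition of the primary outcome. The code list matches neither all stroke nor stroke without I60, and the counting unit changes within one section. The consequence is minor. With 3% to 5% of the denominator affected, a hospital's rate shifts by about 0.2 to 0.3 points at 5% and 0.4 to 0.7 points at 12%, against a planned 7 to 10 points. This amounts to slight extra variation between hospitals and a possible change of stratum or subgroup for a hospital at the boundary. Nothing in the document shows a systematic difference between the arms. The size rests on assumed shares; the existence of the mismatch does not.

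**What to change.** 1. Replace I60.9 with the whole I60 category, which fits the stated all-stroke aim. If subarachnoid haemorrhage is not intended, drop I60.9 and say so, and word the aim and the limitations section to match.
2. State one counting unit, admission or person, and use it in both numerator and denominator.
3. Apply the same code list and unit to the baseline and Year 4 rates. If hospitals are already randomised, leave the strata as allocated.

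The cost is a wording change and a corrected code list in an extraction that is already planned. Baseline rates have to be recomputed once and may shift slightly from those used in planning.
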